# Adjuvant hepatic arterial infusion pump chemotherapy and resection versus resection alone in patients with low-risk resectable colorectal liver metastases – the multicenter randomized controlled PUMP trial

**DOI:** 10.1186/s12885-019-5515-6

**Published:** 2019-04-05

**Keywords:** Colorectal liver metastasis, Resection, Adjuvant chemotherapy, Hepatic arterial infusion, Survival

## Abstract

**Background:**

Recurrences are reported in 70% of all patients after resection of colorectal liver metastases (CRLM), in which half are confined to the liver. Adjuvant hepatic arterial infusion pump (HAIP) chemotherapy aims to reduce the risk of intrahepatic recurrence. A large retrospective propensity score analysis demonstrated that HAIP chemotherapy is particularly effective in patients with low-risk oncological features. The aim of this randomized controlled trial (RCT) --the PUMP trial-- is to investigate the efficacy of adjuvant HAIP chemotherapy in low-risk patients with resectable CRLM.

**Methods:**

This is an open label multicenter RCT. A total of 230 patients with resectable CRLM without extrahepatic disease will be included. Only patients with a clinical risk score (CRS) of 0 to 2 are eligible, meaning: patients are allowed to have no more than two out of five poor prognostic factors (disease-free interval less than 12 months, node-positive colorectal cancer, more than 1 CRLM, largest CRLM more than 5 cm in diameter, serum Carcinoembryonic Antigen above 200 μg/L). Patients randomized to arm A undergo complete resection of CRLM without any adjuvant treatment, which is the standard of care in the Netherlands. Patients in arm B receive an implantable pump at the time of CRLM resection and start adjuvant HAIP chemotherapy 4–12 weeks after surgery, with 6 cycles of floxuridine scheduled. The primary endpoint is progression-free survival (PFS). Secondary endpoints include overall survival, hepatic PFS, safety, quality of life, and cost-effectiveness. Pharmacokinetics of intra-arterial administration of floxuridine will be investigated as well as predictive biomarkers for the efficacy of HAIP chemotherapy. In a side study, the accuracy of CT angiography will be compared to radionuclide scintigraphy to detect extrahepatic perfusion. We hypothesize that adjuvant HAIP chemotherapy leads to improved survival, improved quality of life, and a reduction of costs, compared to resection alone.

**Discussion:**

If this PUMP trial demonstrates that adjuvant HAIP chemotherapy improves survival in low-risk patients, this treatment approach may be implemented in the standard of care of patients with resected CRLM since adjuvant systemic chemotherapy alone has not improved survival.

**Trial registration:**

The PUMP trial is registered in the Netherlands Trial Register (NTR), number: 7493. Date of registration September 23, 2018.

## Background

Colorectal cancer (CRC) is the third most common cancer in the Netherlands. More than half of patients with CRC will eventually develop colorectal liver metastases (CRLM), of whom 25% have resectable disease at first presentation [1]. Most patients develop recurrent disease after curative intent resection of CRLM, which in about 50% of patients is confined to the liver [2]. A large phase III trial investigating perioperative systemic chemotherapy for patients with resectable CRLM found overlapping survival curves: 5-year overall survival (OS) was 51% with perioperative chemotherapy versus 48% with surgery alone (*p* = 0.34) [3, 4]. Therefore, resection without additional chemotherapy is currently the standard of care in the Netherlands and better adjuvant treatment is needed.

The risk of recurrence can be predicted with the clinical risk score (CRS) [5]. The CRS is the sum of five poor prognostic factors: disease-free interval less than 12 months, node-positive CRC, more than one CRLM, largest CRLM over 5 cm in diameter, and serum carcinoembryonic antigen (CEA) level above 200 μg/L. After assigning one point to each of the five risk factors, patients can be stratified into low-risk (0–2 points) and high-risk (3–5 points) of recurrence.

### Hepatic arterial infusion pump chemotherapy

Hepatic arterial infusion pump (HAIP) chemotherapy using floxuridine for liver tumors is a treatment that has been developed at Memorial Sloan Kettering Cancer Center (MSKCC, New York, USA). It is currently not available in the European Union (EU), because floxuridine (FUDR) is not registered in the EU. The biological rationale for intra-arterial treatment is that the hepatic artery rather than the portal vein is responsible for most of the blood supply to liver tumors [6, 7]. Intra-arterial floxuridine is delivered in the hepatic artery via a surgically implantable pump with a catheter in the gastroduodenal artery. Up to 95% of floxuridine is extracted by the liver during the first-pass, allowing an up to 400-fold increase in hepatic exposure with minimal systemic exposure [8, 9]. The pump is filled percutaneously and the liver is continuously perfused with chemotherapy.

Promising results of HAIP chemotherapy have been reported. A randomized controlled trial (RCT) demonstrated superior 2-year overall survival (OS) of 85% in patients with resectable CRLM treated with HAIP and concurrent systemic chemotherapy (5-FU) compared to 69% in patients with resection and systemic chemotherapy (5-FU) only (*p* = 0.02) [10]. A recent retrospective analysis evaluated 2368 consecutive patients undergoing complete resection of CRLM with and without adjuvant HAIP chemotherapy at MSKCC between 1992 and 2012 [11]. The median OS with HAIP chemotherapy was 67 months versus 44 months without HAIP chemotherapy (*p* < 0.001). After adjusting for seven independent prognostic factors in multivariable analysis, the hazard ratio (HR) of HAIP chemotherapy was 0.67 (95% CI: 0.59–0.76, *p* < 0.001) [11]. The median OS in the group without HAIP chemotherapy was similar to the 45 months found in a series of 2715 patients from the UK where no HAIP chemotherapy was used [12]. Subgroup analyses demonstrated that HAIP chemotherapy is particularly effective in low-risk patients (median OS 89 months versus 53 months, *p* < 0.001). In high-risk patients however, the difference in median OS was still statistically significant and clinically relevant, however, less pronounced (50 months versus 37 months, *p* < 0.001) [13].

## Methods/design

### Objective

The primary aim is to compare the progression-free survival (PFS) of surgery with adjuvant HAIP chemotherapy to surgery alone in patients with resectable CRLM with a low CRS 0–2 points). Secondary objectives are to compare OS, postoperative complications, adverse events, quality of life, and costs between the two arms. Pharmacokinetics of intra-arterial administration of floxuridine will be investigated as well as predictive biomarkers for the efficacy of HAIP chemotherapy. In a side study, the accuracy of CT angiography will be compared to radionuclide scintigraphy to detect extrahepatic perfusion.

### Study design

The PUMP trial is a phase III randomized controlled open label, multicenter trial to compare the combined efficacy of resection and/or open ablation and adjuvant HAIP chemotherapy to resection and/or open ablation alone in patients with CRC and resectable CRLM with a low CRS (0–2 points). This trial started in August 2018. Five centers participate in this study (Erasmus MC Cancer Institute, Rotterdam; Antoni van Leeuwenhoek, Amsterdam; Academic Medical Center, Amsterdam; Universitary Medical Center Utrecht, Utrecht; IJsselland Hospital, Capelle aan den IJssel). Patients will be randomized in a 1:1 ratio (Fig. 1) to resection of CRLM only (arm A), or resection of CRLM with adjuvant HAIP chemotherapy (arm B). Stratification factors will be center, number of CRLM (< 4 or ≥ 4 CRLM), and size of the largest CRLM (< 5 cm or ≥ 5 cm). Blinding is not feasible because of the nature of the intervention, including a visible subcutaneous pump. In patients who received preoperative chemotherapy for CRLM, the CRS values prior to start of preoperative chemotherapy should be used to determine eligibility. A computed tomography (CT) scan in (early) arterial phase of the liver is required prior to inclusion to determine whether intra-arterial catheter placement is technically possible. The multidisciplinary meeting should determine that complete resection of the CRLM is feasible. Resectability is defined as the opportunity to achieve an R0 resection with a sufficient liver remnant. Randomization will be performed preoperatively if the participant meets all the criteria.

**Fig. 1 Fig1:**
[figure not shown]
Study flow-chart

### Study population

Adults with resectable CRLM without extrahepatic disease (EHD) and a low CRS (0–2 points) will be considered for inclusion.

Patients are eligible for this study when they meet the following inclusion criteria:age ≥ 18 years;ECOG performance status 0 or 1;histologically confirmed CRC;radiologically confirmed CRLM, amenable for local treatment (resection or open ablation);CRS of 0–2. In patients with unknown nodal status of the CRC (in patients with synchronous resection of CRC and CRLM), the nodal status is counted as zero;positioning of a catheter for HAIP chemotherapy is technically feasible based on an early arterial phase CT angiography (CTA) (1 mm slide thickness);adequate bone marrow, liver, and renal function as assessed by the following laboratory requirements to be conducted within 15 days prior to randomization: absolute neutrophil count (ANC) ≥1.5 × 109/L, platelets ≥100 × 109/L, Hb ≥5.5 mmol/L, total bilirubin ≤1.5 upper normal limit (UNL), ASAT ≤5 x UNL, ALAT ≤5 x UNL, alkaline phosphatase ≤5 x UNL, (calculated) glomerular filtration rate (GFR) >30 mL/min;written informed consent.

A potential subject who meets any of the following criteria will be excluded from participation in this study:presence of EHD, including positive portal lymph nodes, at the time of liver resection or any time since CRC diagnosis, with exception of small (≤ 1 cm) extrahepatic lesions which are not clearly suspicious of metastases (e.g., pulmonary lesions that are too small to characterize);second primary malignancy except in situ carcinoma of the cervix, adequately treated non-melanoma skin cancer, or other malignancy treated at least 5 years prior to inclusion without evidence of recurrence;prior hepatic radiation, resection, intra-arterial therapy or ablation;CRLM requiring two-staged liver resections;liver-first resections; but simultaneous resection of CRC and CRLM is not an exclusion criterion;(partial) portal vein thrombosis;known DPD-deficiency (heterozygous or homozygous of *DPYP*);pregnant or lactating women;history of psychiatric disability judged by the investigator to be clinically significant, precluding informed consent or interfering with compliance for HAIP chemotherapy;serious concomitant systemic disorders that would compromise the safety of the patient or his/her ability to complete the study, at the discretion of the investigator;organ allografts requiring immunosuppressive therapy;serious, non-healing wound, ulcer, or bone fracture;chronic treatment with corticosteroids;serious infections (uncontrolled or requiring treatment);participation in another interventional study for CRLM with survival as outcome;any psychological, familial, sociological, or geographical condition potentially hampering compliance with the study protocol and follow-up schedule.

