## Treatment strategies

### Standard procedures in control arm (arm A)

Patients included in the study should undergo surgery within 6 weeks after signing the informed consent. Local treatment (resection and/or open ablation) of the CRLM in both arms is in accordance with the national guidelines. An intra-operative ultrasound evaluation of the liver will be performed to assure the feasibility of complete resection of the CRLM with an adequate liver remnant. Resection of CRLM can be performed either by minimal-invasive (laparoscopic or robotic) or open approach at the discretion of the surgeon.

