### Investigational procedures of the experimental arm (arm B)

The treatment of patients randomized to the experimental arm consists of HAI pump placement following complete resection and/or open ablation of all CRLM. Pump implantation will be cancelled in patients with unexpected unresectable CRLM or EHD detected at the time of surgery. Implantation of the HAI pump (Tricumed IP2000V infusion pump; Fig. 2) is performed by an open or minimal-invasive approach. In patients requiring simultaneous resection of the primary tumor and CRLM, the colorectal resection is performed after pump placement to reduce the risk of pump contamination. The implantation procedure of the infusion pump and dose adjustment protocols have been discussed by previous authors and was optimized for the materials used in this trial [14, 15]. In addition to local treatment of the CRLM, a cholecystectomy is performed to avoid cholecystitis as a result of inadvertent intra-arterial chemotherapy of the gallbladder [16]. The pump catheter is positioned in the gastroduodenal artery (GDA) allowing perfusion of the entire liver without obstructing the flow in the hepatic artery. The pump catheter has rings at the distal end that allow for securing the catheter with non-absorbable ties in the GDA (Fig. 3). In patients with abnormal hepatic arterial anatomy, the GDA is still the preferred site, as long as it connects with a proper hepatic artery perfusing at least one segment of the liver. Perfusion of the entire liver can be achieved in these patients by ligating all accessory and replaced hepatic arteries. Intrahepatic shunts will typically reassure that the catheter perfuses all liver segments.

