**Fig. 3 Fig3:**

Distal tip of the intra-arterial catheter

The entire GDA and the proximal proper hepatic artery are mobilized and dissected circumferentially from their attachments to facilitate insertion of the catheter and to avoid inadvertent perfusion of the pancreas, stomach, or duodenum. Branches to the retroperitoneum arising from the right or left hepatic artery are common and should be ligated. The use of papaverine is optional to gain additional dilatation of the GDA.

Before implantation, a function test of the pump is performed to confirm flow. The pump pocket should be created in the left lower quadrant so that contact with the anterior superior iliac spine and the lower ribs is avoided. The pocket cavity should be 3/4 caudal to the incision to ensure an optimal position of the septum for refills. The catheter is tunneled through the abdominal wall into the abdominal cavity. The pump is secured to the abdominal fascia with nonabsorbable sutures; the catheter should be positioned behind the pump to prevent catheter injury by a needle when accessing the pump percutaneously.

Next, the GDA is ligated with a nonabsorbable tie as far away (at least 2 cm) from the common hepatic artery as possible. Vascular control of the common and proper hepatic arteries is achieved with vascular clamps or vessel loops. Isolated vascular control of the GDA at its orifice can be used alternatively to avoid occlusion of the hepatic artery. A transverse arteriotomy is made in the distal GDA, and the catheter is inserted up to but not beyond the junction with the hepatic artery (Fig. 4). If the catheter protrudes into the common hepatic artery, turbulence of blood flow can lead to increased risk of thrombosis of the hepatic artery. Failure to pass the catheter to the junction leaves a short segment of the GDA exposed to full concentrations of floxuridine without the diluting effect of blood flow, potentially resulting in sclerosis, thrombosis, pseudo-aneurysm with bleeding, or late dislodgment. When positioned, the catheter should be secured with three to four nonabsorbable ties (silk 2.0) proximal to the tying rings on the catheter. Perfusion of both lobes of the liver and lack of extrahepatic perfusion is confirmed by a bolus injection of methylene blue. After the perfusion test, the catheter is flushed with heparinized saline, and the wounds are closed.

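### The exclusion criterion covers extrahepatic disease found at resection, but randomisation is preoperative and open label, so part of it can be met only after allocation; the arms have no common rule for such patients

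*Protocol article*

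**What the plan says.** Four places in the protocol article bear on this.

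- **Study population, exclusion criteria.** The list opens with "A potential subject who meets any of the following criteria will be excluded from participation in this study". The first criterion is "presence of EHD, including positive portal lymph nodes, at the time of liver resection or any time since CRC diagnosis". Its only exception is for extrahepatic lesions of at most 1 cm that are not clearly suspicious.
- **Study design.** "Randomization will be performed preoperatively if the participant meets all the criteria". The trial is open label: "Blinding is not feasible because of the nature of the intervention".
- **Investigational procedures of the experimental arm (arm B).** "Pump implantation will be cancelled in patients with unexpected unresectable CRLM or EHD detected at the time of surgery". Nothing is said there about the patient leaving the trial. The same section describes a cholecystectomy and, for catheter placement, "The entire GDA and the proximal proper hepatic artery are mobilized and dissected circumferentially from their attachments".
- **Standard procedures in control arm (arm A).** "An intra-operative ultrasound evaluation of the liver will be performed to assure the feasibility of complete resection", and "Resection of CRLM can be performed either by minimal-invasive (laparoscopic or robotic) or open approach at the discretion of the surgeon". No rule is given for EHD found at operation.

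Under Primary endpoint, PFS is counted from surgery, not from randomisation.

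**The concern.** An eligibility criterion has to be decidable when the patient is randomised. Occult EHD, or portal-node status settled in theatre or by pathology, is not. Applied as written, the criterion lets a randomised patient be declared ineligible by a team that knows the allocation.

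The sections also disagree on what follows from the finding. The eligibility list says exclusion from participation, the arm B section says no pump, and the arm A section says nothing. Two identical patients could be handled differently because of their arm. Because PFS starts at surgery, a patient declared ineligible in theatre could easily be treated as never having entered follow-up.

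These patients are likely to do worse than the rest. The Discussion cites retrospective median overall survival of 37 versus 33 months with EHD, against 89 versus 53 months in low-risk patients. Removing more of them from one arm would therefore flatter that arm. The extra arterial dissection and the explicit EHD rule are described for arm B only, so the likelier direction is in favour of pump chemotherapy.

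**Working it through.** **Step 1. The passages side by side**

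| Question | Eligibility list | Arm B section | Arm A section |
|---|---|---|---|
| EHD first found at surgery: what happens? | Excluded from participation | Pump cancelled; exclusion not mentioned | No rule |
| When is it known? | At or after resection | At surgery | Not addressed |
| Is the arm known by then? | Yes: randomised preoperatively, open label | Yes | Yes |

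The contradiction rests on the text alone and needs no arithmetic.

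**Step 2. The plan's own figures**

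Inputs from Sample size calculation: HR 0.60, 80% power, two-sided 5%, control median 17 months, 36 months of accrual plus 12 of follow-up, 5% drop-out.

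- Events (Freedman): (1.960 + 0.842)² × [(1 + 0.60)/(1 − 0.60)]² = 7.849 × 16 = 125.6, so 126, as stated.
- Event probability per arm: 1 − [exp(−12λ) − exp(−48λ)]/(36λ), with λ = ln 2/median. This gives 0.679 for 17 months and 0.504 for 17/0.60 = 28.3 months; the mean is 0.591.
- Patients: 126/0.591 = 213.04, so 214; 214/0.95 = 225.3, so 226, against 230 stated.

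The sample size reproduces, and the point does not depend on it.

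**Step 3. Cost in events if patients were removed equally from both arms**

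The share removed, q, is assumed. Expected events = 230 × 0.95 × (1 − q) × 0.5914; power = Φ(√events × 0.25 − 1.96).

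| q | Events | Power |
|---|---|---|
| 0% | 129 | 81% |
| 5% | 123 | 79% |
| 10% | 116 | 77% |
| 15% | 110 | 75% |

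Equal removal costs some power but causes no bias.

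**Step 4. Bias if removal differed by arm, with a true HR of 1**

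The prevalence f of occult EHD, the median PFS of those patients, and the detection rate r in each arm are all assumptions; the article gives none of them. Patients without EHD have a median of 17 months. After removal, the fraction still at risk in an arm is

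Y(t) = G(t) × [f(1 − r)·exp(−λ_E t) + (1 − f)·exp(−λt)],

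where G(t) is 1 up to 12 months and falls linearly to 0 at 48 months, and d(t) is the matching event density. The apparent log HR, β, solves

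∫ {d_B − (d_A + d_B)·Y_B e^β/(Y_A + Y_B e^β)} dt = 0.

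The two-sided type I error at 126 events is Φ(k − 1.96) + Φ(−k − 1.96), with k = −ln(HR) × √126/2.

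| f | Median PFS with EHD (months) | Detection A 50%, B 50%: HR | A 50%, B 100%: HR (type I error) | A 0%, B 100%: HR (type I error) |
|---|---|---|---|---|
| 5% | 3 | 1.00 | 0.97 (0.053) | 0.94 (0.063) |
| 5% | 6 | 1.00 | 0.98 (0.052) | 0.96 (0.057) |
| 10% | 3 | 1.00 | 0.94 (0.065) | 0.89 (0.104) |
| 10% | 6 | 1.00 | 0.95 (0.058) | 0.91 (0.080) |
| 15% | 3 | 1.00 | 0.91 (0.085) | 0.83 (0.174) |
| 15% | 6 | 1.00 | 0.93 (0.069) | 0.87 (0.117) |

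Example: for f = 10%, 3 months and half detection in arm A, the HR is 0.939, so k = 0.0629 × 11.225/2 = 0.353 and the type I error is about 0.065.

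The last column is an extreme bound, not an expectation. An alternative assumption, a four-fold hazard with EHD (median 17/4 = 4.25 months) at 10% prevalence, gives 0.94 if arm A finds half and 0.92 if it finds a quarter.

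**The case against.** The strongest defence has four parts.

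1. **The list concerns potential subjects, so it governs screening.** The phrase about resection may only date the disease, covering current as well as past EHD, without ordering a second eligibility check in theatre. The exception for small uncharacterised lesions fits preoperative imaging. This is a fair reading, but the text does not secure it: presence at resection is a ground of its own, and the exception does not cover positive portal nodes.
2. **EHD found at surgery is addressed for arm B, and the stated consequence is loss of the pump.** This stands. A reader might infer from the eligibility list that such patients are dropped from the analysis. No section says so, and the arm B text can be read as keeping them in the trial. The analysis population may be defined in the full protocol or analysis plan, neither of which is shown, so its absence here is not held against the article.
3. **Unequal detection is not documented.** A reader might infer that the dissection in arm B finds more EHD. The article does not say this. It describes no portal-node sampling in either arm, places the pump after complete resection, and allows open or minimally invasive surgery in both arms. It describes pump placement in detail and liver resection hardly at all, so silence on dissection in arm A is weak evidence that none occurs. Unequal detection is plausible, no more.
4. **The bias figures rest wholly on assumed inputs.** This also stands. They show what could follow, not what will.

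What survives is the wording: a criterion that can be met only after allocation, and three sections that do not agree on its consequence.

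**Conclusion.** The point holds in a limited form. Taken literally, the exclusion criterion permits exclusion after randomisation on a finding made with the arm known, and it does not match the arm B rule or the silence for arm A. That is a defect in the stated text.

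Bias in PFS would need two further conditions that the article does not establish: that such patients are actually removed, and that detection or handling differs by arm. If both held, with arm B finding all and arm A half of the occult EHD, a true HR of 1 would appear as about 0.91–0.98 and the type I error would be about 0.052–0.085 at 126 events. With equal detection the HR stays at 1.00 and only events are lost. The conclusion that the trial is biased towards pump chemotherapy, or that its randomisation is undone, goes beyond the documents.

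Severity is moderate: worth correcting because the repair is cheap and protects the primary comparison, but not a fatal flaw.

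**What to change.** Reconcile the Study design section, the exclusion criteria and the two surgical sections:

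- Limit the exclusion criterion to EHD, including positive portal nodes, known before randomisation.
- State that EHD or positive nodes first found at or after surgery do not remove a randomised patient, in either arm, from follow-up or from the primary analysis by allocated arm.
- Record operative and pathological EHD findings in the same way in both arms, and report their number by arm.
- Give one PFS event rule, identical in both arms, for randomised patients without complete resection.

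The pump-cancellation rule and all other treatment rules can stay as they are, because the change concerns only eligibility, follow-up and analysis. The cost is one eligibility sentence, one or two sentences on follow-up and analysis, and a field on the operative record. A few EHD-positive patients then remain in both arms and slightly dilute the estimated effect. For example, under the assumed four-fold hazard at 10% prevalence, an HR of 0.75 within both groups of patients appears as about 0.77 when all randomised patients are analysed.
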